### Study groups

2.5

One hundred patients with successful ablation of AF who meet the selection criteria will be divided into 2 groups, namely subjects who develop AF recurrence at 1-year post ablation (group 1) and subjects with no recurrence of AF at 1-year post ablation (group 2).

### Study procedures and outcome assessment

2.6

The following information will be collected from all patients: baseline demographics, history and physical examination findings, cardiovascular risk factors. Conventional 12-lead EGC was performed in each patient at baseline, 1, 3, 6, 12 months follow-up visit.

#### Biomarkers assays

2.6.1

Complete blood count and biochemistry will be evaluated at the central laboratory of the County Clinical Emergency Hospital of Tirgu Mures as per routine clinical practice, at baseline.

Inflammatory status will be assessed at baseline, respectively at 1-year post procedure. hsCRP levels will be assayed by immunoturbidimetric assay (COBAS INTEGRA 400 plus Analyser, Roche Diagnostics, Switzerland). Matrix metalloprotease 9 and interleukin-6 levels will be assessed via enzyme immunoassay (ELISA) method (Dynex DSX Automated ELISA System, Dynex Technologies, USA; IMMULITE 2000 XPi Immunoassay System, Siemens, USA). Determination of all inflammatory biomarkers will be performed at the Advanced Medical and Pharmaceutical Research Center of the University of Medicine and Pharmacy Targu-Mures. NT-proBNP serum levels will be determined prior to the procedure, at 24 hours, and repeated after 1 year, at the central laboratory of the Emergency Clinical County Hospital of Tirgu-Mures using an electrochemiluminescent immunoassay (IMMULITE 2000 XPi Immunoassay System, Siemens, USA).

#### 2D transthoracic echocardiography

2.6.2

All patients will undergo transthoracic echocardiography with simultaneous ECG recording at baseline and 1-year post ablation procedure. Echocardiographic assessment will be performed with a Vivid E9 echocardiographic equipment (General Electric Vingmed Ultrasound, Horten, Norway), at rest, in the lateral decubitus position. Standard M-mode, 2-dimensional and Doppler images will be acquired as per American Society of Echocardiography standards. Left ventricular volumes and ejection fraction will be quantified and calculated according to Simpson rule, using images acquired in the apical 4-chamber plane. All measurements will be averaged for at least 3 heart cycles.

#### Late gadolinium-enhancement cardiac magnetic resonance

2.6.3

All CMR examinations will be performed with an 1.5 T Siemens Magnetom Aera magnetic resonance equipment (Siemens, Erlangen, Germany). LV function will be assessed using cine sequences in long-axis (2-chamber and 4-chamber) and short axis. Short-axis volumetry will be used for determination of LV mass, LV ejection fraction, LV end-diastolic volume (LVEDV) and end-systolic volume (LVESV). Ventricular and atrial fibrosis will be assessed using late postgadolinium myocardial enhancement sequences (LGE) at 10 minutes after intravenous injection of gadolinium extracellular contrast agents. Acquired LGE images will be post-processed using the Medis QMass 8.1 software (Medis, Leiden, the Netherlands) with definition of the epicardial and endocardial contours and manual setting of the hyper-enhancement threshold for the recorded sequence of slices. Delayed signal intensity (DSI) analysis performed in 10 to 12 consecutive short-axis LGE images. The full width at half maximum will be used for image segmentation, using an automated hyper-enhancement threshold and fibrotic areas will be considered those with slow washout kinetic.

Quantification of epicardial fat volume will be performed by tracing and manually adjusting epicardial contours, as part of the post-processing protocols.

#### Ablation protocol

2.6.4

Seldinger technique will be used for venous access, with 1 sheath positioned on the left and 2 sheaths on the right femoral veins. A decapolar diagnostic catheter will be placed in the coronary sinus, after being advanced via left femoral access site and secured with a 6F sheath.

Transesophageal echocardiography will be used to guide interatrial septal puncture. A bolus of 5000 to 7500 U of heparin followed by 1000 to 2000 U/h will be administrated and the following heparin dosage will be adjusted using activated clotting time, determined every 15 to 30 minutes.

In case of radiofrequency ablation, 1 non-steerable sheath will be used for placing the duodecapolar mapping catheter (Lasso) and the other steerable sheath for placing the 3.5 mm tip externally irrigated contact force-sensing ablation catheter. A continuous heparinized saline wash of the long sheaths will be provided during the entire procedure. The 3-D electro-anatomical map will be acquired with the EnSite^TM^ NavX^TM^ system, Model EE3000 (St. Jude Medical, St. Paul, MN, USA), improved by fusing images acquired with CMR images. After inserting the mapping catheter in the ostium of the pulmonary vein (PV), radiofrequency catheter ablation will be performed to obtain pulmonary vein isolation. Ablation will consist in applying a 30 W energy and a 10 to 30 g pressure with temperature adjusted at 50°C, by an irrigated (5–20 ml/min) contact force-sensing catheter positioned on the left atrial wall. A PV will be considered electrically isolated by eliminating all electrical potentials, or by demonstrating successful PV potential dissociation.

In case of cryoablation procedure, a cryoablation balloon (Arctic Front Advance Cryoablation Catheter, Medtronic, Quebec, Canada) will be advanced with transesophageal control via transseptal route and will be placed at the ostium of each pulmonary vein, delivering minus 40 to 70° cooling energy, during 180 to 240 seconds application. The ablation will be considered efficient when complete electrical block between atrial tissue and pulmonary vein will be achieved.

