### Background and rationale

1.1

Atrial fibrillation (AF) has an increasing prevalence, being currently the most frequent type of supraventricular arrhythmia and representing a significant burden for the healthcare system. In most of the cases, myocardial tissue located at the level of the pulmonary veins represents the origin of AF. The pathophysiology of AF is still incompletely understood, several studies suggesting that profibrotic and inflammatory processes can play a crucial role in the development of AF.^[1]^ So far the success rate of AF ablation is not very high, reaching 70% in patients with paroxysmal AF and 50% in cases with persistent AF. Several risk factors for the occurrence and recurrence of AF have been described in the literature, including left atrial (LA) enlargement, left ventricular (LV) dysfunction, the amount of epicardial fat surrounding cardiac structures, or myocardial fibrosis.^[2]^ However, the relationship between inflammatory-mediated myocardial fibrosis and AF recurrence after radiofrequency catheter ablation has not been elucidated so far.^[3]^

Here we present the study protocol of the FIBRO-RISK trial, a prospective, single-center, cohort study which aims to investigate the impact of inflammatory-mediated myocardial fibrosis on the risk of recurrence after successful catheter ablation of AF.

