**Figure 1 F1:**
[figure not shown]
Flowchart diagram of FIBRO-RISK study. hs-CRP = high sensitivity C reactive proteine, IL-6 = Interleukine 6, LGE – CMR = late Gadolinium enhancement CMR, MMPs = matrix metalloproteinases, TTE = transthoracic echocardiography.

Inclusion criteria:

Patients with non-valvular paroxysmal or persistent AF who undergo successful catheter ablation, either by cryoablation or by radiofrequency advanced 3D mapping system;Ability to provide informed consent;Patients aged at least 18 years;

Exclusion criteria:

Patients with valvular AF;Patients with acute coronary syndrome in the last 30 days;Patients in whom AF is presumed to be caused by hyperthyreosis;Patients with long-standing persistent or permanent AF;Unwillingness or incapacity to provide informed consent;Allergy to gadolinium contrast media;Absolute or relative contraindications to magnetic resonance imaging;Pregnancy or lactation;Women with childbearing potential in absence of any contraceptive treatment;Renal insufficiency (creatinine greater than 1.5 mg/dL) or renal failure requiring dialysis;Active malignancy or malignancy within the last 5 year prior to enrollment;Conditions associated with an estimated life expectancy of under 2 years;

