### Data collection

2.11

All the information will be collected in a database that consists of patient's background, medical history, medication, imaging features provided by cardiac ultrasound, CMR and imaging post-processing.

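### Radiofrequency and cryoablation are pooled and markers are compared by unadjusted tests, so the planned analysis cannot show that a marker predicts recurrence independently of modality

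*Protocol article*

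**What the plan says.** **Entry.** The inclusion criteria (section 2.3, after Figure 1) take patients with paroxysmal or persistent AF "who undergo successful catheter ablation, either by cryoablation or by radiofrequency advanced 3D mapping system". The article states no rule for assigning a patient to one technique or the other.

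**Procedures.** Section 2.6.4 gives each technique its own delivery. For radiofrequency: "Ablation will consist in applying a 30 W energy and a 10 to 30 g pressure with temperature adjusted at 50°C". For the cryoballoon: "delivering minus 40 to 70° cooling energy, during 180 to 240 seconds application".

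**Groups and tests.** Sections 2.3 and 2.5 divide patients only by whether AF recurs within one year. Section 2.13 names a t test or Mann-Whitney test for continuous variables and Fisher's exact test for categorical ones. It names no covariate and no stratum.

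**Aim.** The Discussion says that the study is to validate ventricular remodelling, serum biomarkers and CMR fibrosis as independent predictors of recurrence.

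**Timing of the markers.** Section 2.3 places hsCRP, MMPs, IL-6 and NT-proBNP in the first 24 hours after the procedure. Section 2.6.1 places the inflammatory markers at baseline and at one year, and NT-proBNP before the procedure, at 24 hours and at one year.

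**The concern.** An unadjusted two-group test shows whether a marker differs between patients with and without recurrence. It does not show whether the marker carries information beyond other features that differ between the groups. Modality is one such feature, and it is not randomised. AF type is another: section 1.1 itself gives different success rates for paroxysmal and persistent AF.

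Suppose that one modality goes with more recurrence, for instance because persistent AF is treated more often with it, and that the same modality goes with a higher marker level. A marker with no predictive value within either modality would then differ between the recurrence groups. The study could report as an independent predictor something that only reflects which catheter was used. A sample taken after the procedure is the likeliest to carry such a difference, because the two procedures act on the tissue differently. A marker measured before the procedure could be affected only through how modality is chosen.

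**Working it through.** **The plan's own figure.** Section 2.12 states 90% power with 50 per group for an event-free proportion of 0.60 and an increase of 0.29, at two-sided alpha 0.05. The exact power of Fisher's test for 0.60 against 0.89 is 90.2%, so the figure reproduces. Nothing below depends on it.

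**Inputs from the document.**
- N = 100 (section 2.12).
- Overall recurrence 40%: the upper end of the 35% to 40% in the Abstract, and 1 − 0.60 from section 2.12.
- Success 70% in paroxysmal and 50% in persistent AF (section 1.1), that is, recurrence of 30% and 50%.

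**Assumptions, not in the document.**
- Half of the patients receive each modality.
- Recurrence is r₁ in one modality and r₂ in the other.
- The marker mean differs by δ SD between modalities, and within each modality the marker is unrelated to recurrence.

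**Spurious difference between recurrence groups.** Let p = (r₁ + r₂)/2. The share of modality 1 is a = 0.5·r₁/p among patients with recurrence and b = 0.5·(1 − r₁)/(1 − p) among those without. The expected difference in marker means is δ·(a − b).

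For r₁ = 0.50, r₂ = 0.30, δ = 1:
- a = 0.25/0.40 = 0.625 and b = 0.25/0.60 = 0.417, so the difference is 0.208 SD.
- Variance is 1 + 0.625 × 0.375 = 1.234 with recurrence (about 40 patients) and 1 + 0.417 × 0.583 = 1.243 without (about 60).
- SE = √(1.234/40 + 1.243/60) = 0.227, and z = 0.208/0.227 = 0.917.
- Rejection = P(Z > 1.96 − 0.917) + P(Z < −1.96 − 0.917) ≈ 0.149 + 0.002 = 15.1%.

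**Simulation** (8,000 trials per row; planned t test, and a linear model with modality added):

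| Recurrence by modality | δ (SD) | Unadjusted | With modality term |
|---|---|---|---|
| 40% / 40% | 1.0 | 5.3% | 4.9% |
| 45% / 35% | 0 | 4.9% | 5.0% |
| 45% / 35% | 0.5 | 6.0% | 5.1% |
| 45% / 35% | 1.0 | 7.6% | 5.0% |
| 50% / 30% | 0 | 5.1% | 5.1% |
| 50% / 30% | 0.5 | 7.8% | 5.0% |
| 50% / 30% | 1.0 | 15.8% | 5.2% |

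The 15.8% agrees with the formula up to approximation and simulation error.

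**How extreme is 50% against 30%?** Those are rates by AF type. They become rates by modality only if every persistent case receives one technique and every paroxysmal case the other. With partial alignment the gap shrinks. At 80/20 the rates are 0.8 × 50 + 0.2 × 30 = 46% and 0.2 × 50 + 0.8 × 30 = 34%. Simulated rejection of the unadjusted test (20,000 trials):

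| AF type to modality | Recurrence | δ = 0.5 | δ = 1 |
|---|---|---|---|
| 80/20 | 46% / 34% | about 6% | about 9% |
| 70/30 | 44% / 36% | about 5.5% | 6.5% |
| 60/40 | 42% / 38% | about 5% | 5% to 6% |

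**The case against.** The strongest reply is that the bias needs two links, from modality to recurrence and from modality to the marker, and the documents establish neither. The 16% requires perfect alignment of modality with AF type and an undocumented 1 SD shift. In that scenario AF type is the source of the recurrence gap, so adjusting for modality alone would treat a proxy. It can also be said that covariates are commonly left to the analysis plan. The first part stands: it limits the size, and it puts AF type into the fix. The second stands only in part. The article does not leave the method open: it names unadjusted tests and, in the same text, an aim that they cannot meet.

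A reader might also infer stronger faults that the documents do not support:

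- *The database holds no ablation data, so the modalities can never be separated.* Section 2.11 says "All the information will be collected in a database that consists of patient's background, medical history, medication, imaging features", and the list does not name modality. But it also omits the serum biomarkers and the ECG and Holter results, which the study plainly records. It is not exhaustive, and sections 2.9 and 2.10 name both techniques as study procedures.
- *The success definitions select different patients.* For radiofrequency the text reads "A PV will be considered electrically isolated by eliminating all electrical potentials, or by demonstrating successful PV potential dissociation". For cryoablation it reads "The ablation will be considered efficient when complete electrical block between atrial tissue and pulmonary vein will be achieved". The wording differs, but both describe acute electrical isolation of the vein, and nothing shows that different patients would qualify.
- *The different energy settings are a defect.* They are inherent in two technologies.
- *The population contradicts the rationale.* Section 1.1 does say that "the relationship between inflammatory-mediated myocardial fibrosis and AF recurrence after radiofrequency catheter ablation has not been elucidated so far". This is one background phrase, and the aim in the same section speaks of catheter ablation in general.

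**Conclusion.** The concern holds as a mismatch between aim and analysis. Two non-randomised modalities are pooled, patients are grouped only by recurrence, and the stated tests adjust for nothing, so they cannot support a claim of independent prediction.

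Whether bias will occur, and how much, cannot be read from the documents. With an even split, recurrence gaps of 10 to 20 points and marker shifts of 0.5 to 1 SD, the 5% error rises to about 6% to 16%. The top of that range is close to a worst case, and partial alignment of modality with AF type gives about 5% to 9%. If either link is absent the error stays near 5%. With modality in the model it stays at about 5% throughout. The risk is greatest for markers drawn within 24 hours after the procedure.

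**What to change.** In section 2.13, analyse each marker's association with recurrence adjusted for, or stratified by, modality and AF type. Examples are a regression with both terms, or a van Elteren test in place of Mann-Whitney. In section 2.11, name modality among the recorded variables. Leave the ablation settings as they are.

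The cost is one recorded field, two analysis terms and possibly software other than the package named in section 2.13. If modality proves unrelated to recurrence, precision falls slightly. The expected squared chance correlation between two unrelated variables in 100 patients is 1/99, so the variance of the marker comparison rises by about 1% for the modality term.

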### Study time

2.7

The clinical trial will be conducted from January 2019 to December 2020.

### Outcomes

2.8

The *primary outcome* of the study is represented by the rate of AF recurrence at 1-year post ablation, documented by either ECG or Holter monitoring.

*Secondary outcome* refers to rate of re-hospitalization, rate of survival without relapse and rate of major adverse cardiovascular events (MACE rate, including cardiovascular death or stroke)

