### Sample size

2.12

The study will include 100 subjects with AF undergoing successful ablation of pulmonary veins via interventional route. After analysis of follow-up data, patients will be distributed in two groups according to the presence or absence of recurrent episodes of AF during the follow-up.

Sample size calculation was performed using the StatMate 2.0 software. For sample calculation, the proportion of event-free population was estimated at 60%. According to this calculation, a sample size of 50 patients in each subgroup has a 90% power to detect an increase in MACE-free rates proportion of 0.29, with a significance level (alpha) of 0.05 (2-tailed). Therefore, the total sample size was established at 100 patients.

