### Statistical analysis

2.13

Statistical analysis will be performed using Graph Pad InStat 3.10 software at the level of significance 5%. All data will be checked for normality. Continuous variables with normal distribution will be presented as mean ± standard deviation and will be compared using *t* test. Non-normally distributed variables will be analyzed using the Mann-Whitney test. Categorical variables will be expressed in numbers and percentages and will be compared using the Fisher exact test.

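### Read literally, the sample size rests on comparing MACE between groups defined by AF recurrence during follow-up, which makes recurrence look protective when it has no effect

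*Protocol article*

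**What the plan says.** Study groups (2.5) defines the only two groups in the article: "subjects who develop AF recurrence at 1-year post ablation (group 1) and subjects with no recurrence of AF at 1-year post ablation (group 2". Sample size (2.12) confirms that they are formed afterwards: "patients will be distributed in two groups according to the presence or absence of recurrent episodes of AF during the follow-up".

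The next paragraph of Sample size gives the calculation: "According to this calculation, a sample size of 50 patients in each subgroup" has 90% power to detect a rise of 0.29 in the MACE-free proportion, from an event-free proportion of 60%, at two-sided alpha 0.05. No other subgroups appear in the article.

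Outcomes (2.8) makes the primary outcome "the rate of AF recurrence at 1-year post ablation, documented by either ECG or Holter monitoring", which is the same event that forms the groups. The secondary outcomes are "rate of re-hospitalization, rate of survival without relapse and rate of major adverse cardiovascular events", with the last described as "MACE rate, including cardiovascular death or stroke". They are listed as rates, and this section names no comparison.

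Statistical analysis (2.13) gives the t test, the Mann-Whitney test and, for categorical variables, says that they "will be compared using the Fisher exact test". It names no time-to-event or time-dependent method.

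**The concern.** Recurrence happens after ablation, yet it is used as if it were a group known on the day of ablation. To enter group 1 a patient must stay alive until AF recurs. A patient who dies of a cardiovascular cause first can only be in group 2. The time before recurrence is thus free of death by construction in group 1 (immortal time), and early deaths collect in group 2.

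At stake is the comparison on which the 100 patients are justified. It would favour recurrence even if recurrence had no effect on death or stroke. It also misses the secondary objective (1.2), which asks how atrial remodelling, epicardial fat and inflammatory markers affect long-term outcomes. A contrast between recurrence groups makes recurrence the exposure and leaves those markers out.

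**Working it through.** **1. The plan's own figure.** Inputs from Sample size: 0.60 versus 0.60 + 0.29 = 0.89, 50 per group, two-sided alpha 0.05. Power is 90.2% by exact enumeration of Fisher's test, 88.6% by the normal approximation with continuity correction, and 92.6% without it. The stated 90% is reproduced. With the split implied by the 35% to 40% recurrence in the Abstract, Fisher power is 89.3% (35/65) or 90.9% (40/60). The arithmetic is not the problem; the choice of groups is.

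**2. Set-up for the bias.** From the article: one-year recurrence R = 35% or 40%. Assumed, because the article gives no figures: one-year cardiovascular death D, one-year non-fatal stroke S, constant hazards, and no effect of recurrence on either.

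- Hazards: a = −ln(1 − R) for recurrence, b = −ln(1 − D) for death.
- Share in group 1 (recurs within the year and before death): A = a/(a + b) × [1 − (1 − R)(1 − D)]. Share in group 2: B = 1 − A.
- MACE risk in group 1: 1 − R(1 − D)(1 − S)/A.
- MACE risk in group 2: 1 − (1 − R)(1 − D)(1 − S)/B.

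**3. One case in full**, R = 0.40, D = S = 0.05:

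- a = 0.5108, b = 0.0513, and 1 − 0.60 × 0.95 = 0.43.
- A = 0.5108/0.5621 × 0.43 = 0.3908, so B = 0.6092.
- Group 1: 1 − 0.3610/0.3908 = 7.6%.
- Group 2: 1 − 0.5415/0.6092 = 11.1%.
- Risk ratio 0.685, although the true ratio is 1.00.

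**4. Range.**

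| R | D | S | MACE, group 1 | MACE, group 2 | Risk ratio | Gap (points) |
|---|---|---|---|---|---|---|
| 35% | 1% | 1% | 1.5% | 2.2% | 0.69 | 0.7 |
| 35% | 2% | 3% | 4.0% | 5.4% | 0.75 | 1.4 |
| 35% | 5% | 5% | 7.6% | 10.9% | 0.70 | 3.3 |
| 40% | 1% | 1% | 1.5% | 2.3% | 0.67 | 0.7 |
| 40% | 2% | 3% | 4.1% | 5.5% | 0.74 | 1.5 |
| 40% | 5% | 5% | 7.6% | 11.1% | 0.69 | 3.5 |

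A simulation of 4 million patients per scenario gives 0.67 to 0.74 and agrees with each row to within 0.01. Unequal mixes widen the range, because only death creates the bias. By the same formulas at R = 40%, D = 1% with S = 5% gives 0.88, and D = 5% with S = 1% gives 0.51.

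**5. Every event fatal.** With S = 0, D = 5% and R = 40%, the risks are 2.75% and 6.44%, ratio 0.43.

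**6. Relapse-free survival, if it were compared between the groups.** By definition it is 0% in group 1 and 100% minus deaths in group 2. No data are needed to know the result.

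**The case against.** **The MACE label may be a slip.** MACE is tied to the subgroups in one sentence only. A 60% event-free proportion would mean 40% with cardiovascular death or stroke within a year if MACE is taken as Outcomes describes it, whereas 60% is the complement of the 40% recurrence in the Abstract. The authors may have meant recurrence-free. This stands as a real ambiguity, but it does not rescue the passage: a recurrence-free proportion cannot be compared between groups formed by recurrence. Either way the endpoint and the groups must be restated.

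**A reader might infer that all secondary outcomes are tested between groups 1 and 2.** The article does not say so. Outcomes lists rates, the text on what is examined in the two groups concerns biomarkers, fibrosis and epicardial fat, and Fisher's test is not assigned to any endpoint. Relapse-free survival or re-hospitalisation reported for the whole cohort fits the wording equally well.

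**A reader might take 0.43 as the size of the bias.** It applies only if every MACE is terminal. Stroke is part of MACE, and a non-fatal stroke neither prevents a later recurrence nor forces a patient into group 2.

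**The absolute effect is small.** At 1% death and 1% stroke about two events are expected in 100 patients. Recurrence concentrated early in the year would shrink the bias further. Both points stand and limit the weight of the finding.

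How patients lost before 12 months are classified is ordinary analysis-plan detail and is not held against the article.

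**Conclusion.** The point holds for MACE. Taken at its word, the article sizes the study on a fixed comparison of MACE-free proportions between groups defined by a later event, and deaths before recurrence can fall only in group 2. With no true effect the risk ratio is about 0.67 to 0.75 in the scenarios tabulated, with a gap of 0.7 to 3.5 percentage points in favour of recurrence. The direction follows from the design. The size rests on assumed death and stroke risks, constant hazards and the 35% to 40% recurrence in the Abstract.

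For relapse-free survival the point is conditional: a test between these groups would be circular, but none is stated. Comparing baseline markers between patients with and without recurrence, which serves the primary objective, is not touched by this finding.

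**What to change.** - Do not test MACE, relapse-free survival or re-hospitalisation between groups 1 and 2.
- Analyse them in the whole cohort from the day of ablation, against the baseline markers named in Study objectives: atrial remodelling, epicardial fat and inflammatory markers for the secondary objective, and fibrosis for the primary. Use time-to-event methods for relapse-free survival, and describe MACE by counts because few events are likely.
- If MACE is to be related to recurrence, enter recurrence as a time-dependent variable, so that a patient counts as recurrent only from the date of recurrence.
- Restate the endpoint in Sample size, and the groups or marker it is compared across, to match.

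The cost is somewhat more analysis work and recording the dates of recurrence, events and last contact. The visits at months 1, 3, 6 and 12 already collect ECG and history, so no assessment is added. One limit remains: a recurrence found only at a scheduled visit is dated no more closely than the interval since the previous visit, and the analysis should allow for this.
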